##### Measurements

Participants in both conditions receive online questionnaires at baseline, and at 6 and 12 months of follow-up. Additionally, a subgroup of the participants will be asked to wear a triaxial accelerometer for 7 days at baseline and 12 months (Fig. 3). The study population will include participants from various educational backgrounds. To ensure that all participants, including those with low (health) literacy, will be able to understand and complete the questionnaire, the questionnaire will be simplified. To maintain the validity of the questionnaire, the nature of the questions will not be adjusted. Words that might be difficult to read or understand will be replaced by better readable and understandable words.

**Fig. 3 Fig3:**
[figure not shown]
Time schedule of the C-RCT

##### Handling and storage of data

Data will be collected by online questionnaires and triaxial accelerometry. Data will be handled confidentially and in compliance with the General Data Protection Regulation (in Dutch: AVG). Raw anonymised data from the accelerometers will be analysed by the UKK Institute in Finland, a processing agreement is drawn up and signed for this purpose. Facilities for storage and back up of the data of the National Institute of Public Health and the Environment (Rijksinstituut voor Volksgezondheid en het Milieu) will be used. Daily backups are made. To ensure confidentiality, data will be pseudonymised. The unique pseudonym for every participant will not be based on the participant’s initials and birth date. A secured database, only accessible for the RIVM researchers involved in this study, will include the link between personal data and the specific pseudonym. At the end of the project, contact data and names of participants will be deleted form this database. Other data will be preserved for 15 years after the project ended. Due to the expected absence of (high) risks for participants of this study, the establishment of a data monitoring committee is not necessary.

###### Primary outcome measure

Lifestyle

Overall lifestyle behavior will be measured with the reliable and validated Simple Lifestyle Indicator Questionnaire (SLIQ) [32, 34]. The SLIQ provides a global lifestyle score and consists of five components: nutrition (3 questions), physical activity (3 questions), alcohol consumption (3 questions), smoking status (2 questions), and stress (1 question) [32]. The Cronbach alphas measured for nutrition and physical activity were 0,58 and 0,60 respectively [32]. As the SLIQ is only available in English it will be translated to Dutch according to the back translation method, derived from the guidelines of Guillemin et al. [35]. Two translators will independently translate the SLIQ from English to Dutch. An independent translator and one of the researchers (DS) will compose a consensus version. This Dutch translation will be back translated to English by two other translators, who are unaware of the original SLIQ. Again a consensus translation will be composed by the same independent translator and researcher. The original SLIQ and the back translated English version will then be compared and changes will be made to the Dutch SLIQ if necessary. Furthermore, cultural adaptations will be made, e.g. examples of physical activity will be adjusted if a sport is not common in the Netherlands. For each lifestyle component in the SLIQ, a score of 0–2 is assigned yielding a total score of 0–10 for the overall lifestyle score, where 0 stands for the most unhealthy lifestyle and 10 the most healthy lifestyle possible.

###### Secondary outcome measures

Secondary outcome measures include physical activity (both occupational and non-occupational), nutrition, sleep, stress, work-life balance, need for recovery, perceived general health, and well-being.

###### Physical activity

A subgroup of participants in both the intervention and control condition will be asked to wear a triaxial accelerometer (RM42 or Actigraph GT9X Link) to objectively measure physical activity at baseline and at 12 months. Participants will wear the same accelerometer at baseline and 12 months. Total minutes of both occupational and non-occupational light, moderate and vigorous activity per day will be measured as well as total minutes of occupational and non-occupational sedentary behavior, i.e. sitting and lying, and number of breaks from sitting per day. Participants will be asked to wear the accelerometer device for 24 hours on 7 consecutive days on their hip [36]. They will also keep a diary to note the date, wearing time, sleep time, working time, and time spent cycling or exercising. Raw acceleration data measured will be analyzed by using the validated mean amplitude deviation (MAD) and angle for posture estimation (APE) algorithms or the Actilife 6 Software [37–39]. Additionally, the valid and reliable Short QUestionnaire to Asses Health-enhancing physical activity (SQUASH) will be included in the questionnaire at baseline, 6 and 12 months [40]. The SQUASH questionnaire measures habitual physical activity levels during a regular week in the past month of four different physical activity domains: commuting, occupational, household and leisure time [40]. For each domain, employees will be asked to indicate the frequency (days per week), self-reported intensity (light, moderate or vigorous) and average duration (hours and minutes) of the activity per day. For each domain, activities will be subdivided into three age-dependent intensity categories (i.e., light/moderate/vigorous), corresponding to the metabolic equivalents (METs) derived from Ainsworth’s compendium of physical activities. Total minutes per week of moderate-to-vigorous physical activities will be calculated by summing the time spent on at least moderate intensity activities across the three domains of commuting, household and leisure time. Moreover one question regarding sedentary behavior will be added, to gain insight in the time spend sitting on an average day (hours and minutes).

###### Nutrition

Nutrition will be measured using six questions derived from the PIAMA Birth Cohort study [41]. One question focuses on the average amount of sugary drinks consumed per week during a regular month. The other questions involve consumption of small and large snacks, both sweet, savory and deep-fried, measuring the average amount of snacks consumed per week during a regular month.

###### Sleep

The Medical Outcomes Study Sleep scale (MOS-SS), a reliable and valid measurement instrument, will be used to assess important aspects of sleep perceived by participants [42]. In total eight aspects of sleep can be measured with the MOS-SS. For this study four aspects will be measured, i.e. sleep quantity, optimal sleep, sleep disturbance, and somnolence. Sleep quantity is scored by the average hours of sleep per night for the last 4 weeks. When a participant reports 7–8 hours of sleep, it is considered as optimal sleep, which leads to a score of 1 on this scale, more or less hours of sleep lead to a score of zero. Sleep disturbance and somnolence are scored on a 6 point scale and converted to a score between 0 and 100, in which a higher score indicates more of the concept being measured. In addition, sleep quantity, time to fall asleep and waking up during sleep will be measured using the triaxial accelerometer.

###### Stress

Stress will be measured using the stress sub-scale of the short version of the Depression Anxiety and Stress Scale (DASS-21) [43]. The stress sub-scale of the DASS-21 consists of seven statements, measuring overall stress during the past week. Responses will be summed into a scale score ranging from 0 to 21, with a higher score representing more stress. Validation of the DASS-21 has been performed in a non-clinical setting [44]. The Cronbach alpha measured for stress was 0,84 [44].

###### Work-life balance

The work-life balance will be measured by the short version of the negative work-home interference scale of the Survey Work-home Interference Nijmegen (SWING), a valid and reliable instrument with a Cronbach alpha of 0,85 [45, 46]. This scale consists of 4 items for which participants are asked to indicate how often their work-life negatively interferes with their home-life on a 4-point scale (0–3). Scores will be summed and averaged, resulting in a score between 0 and 3, in which 3 is the most negative work-home interference possible.

###### Need for recovery

Need for recovery will be measured using the corresponding subscale of the Questionnaire on the Experience and Evaluation of Work [47] The need for recovery scale is valid for the measurement of (early symptoms of) fatigue after work and a Cronbach alpha of 0,88 was measured [48]. The scale consists of 11 questions to be answered on a dichotomous scale (yes/no). The total score is standardized to a score between 0 and 100, in which 100 represents the highest need for recovery.

###### General health

Perceived general health will be measured using the subscale ‘general health perceptions’ of the RAND-36, which is a widely used and validated instrument to measure health-related quality of life [49]. The Cronbach alpha of the general health perception subscale was 0.81 [49]. General health is measured by 5 items on a 5 point scale. Answers will be coded, summed, and then transformed to a 0 to 100 scale with a higher score indicating a better health status.

###### Well-being

Well-being will be assessed by the 5-item World Health Organization Well-Being Index (WHO-5), which has shown good construct validity in various settings [50]. The questionnaire consists of five statements to be answered on a 6 point rating scale (0–5). The total score (0–25) is multiplied by 4 to achieve a scoring of 0–100 where 100 represents the best imaginable well-being.

###### Potential confounders and effect modifiers

Data on potential confounders and effect modifiers will be assessed by questionnaire including age, gender, highest educational level attained, marital status, type of work (blue/white collar), working conditions (i.e. working from home), and working days and hours per week.

##### Data analysis

First, descriptive statistics (means, standard deviations, or frequencies) at baseline will be performed for all relevant variables. The effect of the Dutch WHPP on the primary and secondary outcomes will be determined by performing longitudinal linear mixed models, adjusting for baseline differences of the outcome measure. Differences in the primary and secondary outcomes at 6 and 12 months between the WHPP condition and the control condition will be analyzed. Main analyses will be performed following the intention-to-treat principle including all available data of the participants regardless their compliance to the program.

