#### Step 5. Implement

Several organizations will participate in the C-RCT to evaluate the Dutch WHPP. As part of the evaluation, the program will initially only be implemented in a randomly selected half of the participating departments or locations, depending on the structure of the organization. The remaining participating departments or locations will serve as a waiting list control condition and will receive the WHPP once the trial has ended.

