##### Randomization and blinding

Randomization within each organization will take place at cluster level and after baseline measurements. Two independent researchers will be involved in the randomization process. The first independent researcher will assign consecutive numbers to all of the clusters within an organization. The second independent researcher will receive this list without being informed about which number corresponds with which cluster. This researcher will use a computer program to randomly assign the numbers to the intervention or control condition [31]. The first independent researcher will receive the list with numbers and their allocation to the intervention or control condition and will link this to the clusters within the organization. Then, the research team of the current study will send the program to the clusters in the intervention condition. However, the researcher involved in the data processing and analyses will be blinded for group allocation, because clusters will be re-coded by an independent researcher prior to analyses.

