##### Sample size calculation

The sample size needed for the proposed study was based on finding an effect on the primary outcome, a combined lifestyle score as measured using the Simple Lifestyle Indicator Questionnaire (SLIQ) [32]. The sample size calculation was carried out including cluster correction using an estimated intra-cluster correlation coefficient (ICC) of 0.04 [33]. Based on a mean score of 7.02 (standard deviation of 1.5) on a scale of 0–10, a power of 80%, a two-sided alpha of 0.05 and an estimated number of 6 clusters per condition, 264 participants (132 per group) are needed to statistically demonstrate an effect on lifestyle of 10%. Taking into account a loss to follow-up of 20% after 12 months, a total of 330 employees (2 groups of 165) need to be included.

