The chosen study design for the effectiveness evaluation, i.e. a C-RCT, is common in public health research [55, 56]. However, it comes with methodological limitations, such as risk of selection and dilution bias and participants within one cluster that tend to be more alike compared to participants in other clusters, and can therefore not be assumed to be independent [30, 57]. In this study we account for this in the design by letting recruitment take place before randomization of the clusters and in the analysis by performing longitudinal multilevel analyses according to the intention-to-treat principle [57, 58]. The study design allows for single blinding, in which the researcher involved in the analyses will be blinded for group allocation. This is a strength of the proposed study.

Overall, literature regarding the adaptation of WHPPs is scarce. Therefore, a process evaluation is valuable as it will provide insight into the success as well as failure aspects of the translation to the Dutch WHPP and its implementation [59]. Results from the process evaluation can thus be used to further improve the implementation plan, that is part of the Dutch WHPP, and to improve program outcomes [60].

The Lombardy WHP Network, an integrated approach for health promotion at the workplace is proven to be effective in the improvement of lifestyle behaviors. However, further scientific evidence about the effectiveness of an integrated approach in the occupational setting is scarce. Following the MAP approach, the good practice Lombardy WHP Network will be systematically tailored to the Dutch context, retaining its core elements. Next, effectiveness and process of implementation will be evaluated. This proposed study to the effectiveness and implementation process of the tailored integrated Dutch WHPP will contribute to filling the gap in literature and practice regarding integrated WHP approaches.

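### Clusters are randomised within each organisation, but the effect model names only the baseline outcome; run as stated, it overstates the standard error where organisations differ

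*Protocol article*

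**What the plan says.** Under Randomization and blinding, the protocol article states: "Randomization within each organization will take place at cluster level and after baseline measurements". Step 5 (Implement) adds that the program first goes to "a randomly selected half of the participating departments or locations, depending on the structure of the organization". Organisation is therefore a stratum, and each one contributes clusters to both arms. The number of organisations is not fixed: "Several organizations will participate in the C-RCT to evaluate the Dutch WHPP". The Abstract says they will come from different industry sectors.

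The Data analysis section of the effect evaluation specifies "longitudinal linear mixed models, adjusting for baseline differences of the outcome measure" for primary and secondary outcomes. It names no other adjustment and no random effects. The Discussion says that the likeness of participants within a cluster is dealt with "in the analysis by performing longitudinal multilevel analyses according to the intention-to-treat principle". Study design defines clusters as working locations or units, so this statement concerns the randomised unit and not the organisation.

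The sample size uses "an estimated intra-cluster correlation coefficient (ICC) of 0.04", a single value that is not divided between organisations and units within them.

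**The concern.** When randomisation is balanced within organisations, a stable difference between organisations affects both arms alike and drops out of the treatment contrast. A model that treats all clusters as exchangeable still counts that difference as noise. The estimated standard error then exceeds the true one, the confidence interval is too wide, and the test rejects less often than its nominal level. Organisations from different sectors, with different shares of blue- and white-collar work, could plausibly differ in lifestyle. With about 12 clusters, precision gained from the stratified design is worth keeping. Leaving the choice open also leaves room to decide after the data are seen whether organisation enters, and that can move the standard error and the P value.

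**Working it through.** **Inputs from the article (Sample size calculation).** "Based on a mean score of 7.02 (standard deviation of 1.5) on a scale of 0–10"; effect 10%; "a power of 80%, a two-sided alpha of 0.05"; ICC 0.04; 6 clusters per condition; 132 per group; 20% loss to follow-up.

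**The plan's own figure.**
- Effect: 0.10 × 7.02 = 0.702 points, or 0.702/1.5 = 0.468 SD.
- Unclustered size per arm: n0 = 2 × (1.5 × (1.960 + 0.842)/0.702)² = 71.67.
- With 6 clusters per arm: n = n0(1 − ICC)/(1 − n0 × ICC/6) = 71.67 × 0.96/(1 − 0.4778) = 131.76, rounded up to 132. That is 22 per cluster, with design effect 1 + 21 × 0.04 = 1.84.
- Loss to follow-up: 264/0.8 = 330.

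The stated numbers reproduce exactly and do not depend on whether organisation is in the model.

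**Standard error with and without organisation.** Assumptions, because the article does not give them: 12 equal clusters of 22; 2, 3 or 6 organisations, balanced by arm; total ICC fixed at 0.04; a share s of it between organisations. With SD² = 2.25, the between-organisation variance is vo = 0.04 × s × 2.25, the within-organisation cluster variance is vc = 0.04 × (1 − s) × 2.25, and the individual variance is ve = 0.96 × 2.25 = 2.16.
- True variance of a cluster mean around its organisation: v = vc + ve/22. True SE of the arm difference: √(2v/6).
- If organisation is omitted, the expected variance is v + vo × (fraction of the 15 within-arm cluster pairs that come from different organisations).

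Worked case, 3 organisations and s = 0.5: vo = vc = 0.045; v = 0.045 + 0.0982 = 0.1432; true SE = √(0.2864/6) = 0.2185. Of the 15 pairs, 12 are from different organisations: 0.1432 + 0.045 × 12/15 = 0.1792; SE = 0.2444. Ratio = 1.12.

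Ratio of the expected SE without organisation to the true SE:

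| Share s | 2 organisations | 3 | 6 |
|---|---|---|---|
| 0 | 1.00 | 1.00 | 1.00 |
| 0.25 | 1.04 | 1.05 | 1.07 |
| 0.5 | 1.09 | 1.12 | 1.15 |
| 0.75 | 1.16 | 1.20 | 1.25 |

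**Type I error and power, no baseline adjustment** (40,000 simulated trials per scenario, t-tests on cluster means). Type I error without organisation is about 5.0% at s = 0, 2.9-3.9% at s = 0.5 and 2.1-3.2% at s = 0.75. With organisation it is 4.8-5.2% throughout.

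| Organisations, share | Power without | Power with |
|---|---|---|
| 3, s = 0 | 0.716 | 0.691 |
| 3, s = 0.5 | 0.757 | 0.806 |
| 3, s = 0.75 | 0.776 | 0.862 |
| 6, s = 0 | 0.715 | 0.616 |
| 6, s = 0.25 | 0.726 | 0.670 |
| 6, s = 0.5 | 0.739 | 0.733 |

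Power is below 80% at s = 0 because these tests use the t distribution on few cluster degrees of freedom, while the sample size formula uses the normal approximation.

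**With the baseline adjustment that the article states.** Stable organisation differences appear at baseline too, so the adjustment removes part of them. One simulation used 3 organisations, individual baseline to follow-up correlation 0.5-0.7, and organisation and cluster effects correlated 0.9-1.0 over time (all assumed). At s = 0.5 the SE ratio is 1.00-1.05, type I error without organisation is 3.8-4.6%, and power with and without organisation differs by at most 0.7 points. At s = 0.75 type I error is 3.5-4.1%. A second simulation, with several assumed organisation counts, gave 3.3-4.3% at s = 0.5. In it, adding organisation changed power by about +1 point for 2-3 organisations and by −2 to −4 points for six organisations of two clusters each.

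**The case against.** The strongest reply is that silence is not exclusion. The Data analysis section does not say that baseline is the sole term, it lists no random effects at all, and the Discussion promises a multilevel analysis whose levels are not spelled out. A journal article often leaves the full model to a longer document. That stands to this extent: a reader might infer that the stratification is ignored, and the article does not establish that. It does not answer the point fully. The article chose to state an adjustment, the stratum is missing from it, and the multilevel statement is offered only as the answer to dependence within clusters.

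The absence of organisation from the list of potential confounders proves little. That list covers questionnaire items, and organisation is already known from recruitment and the randomisation list.

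A reader might also infer a sizeable loss of power, such as 76% against 81% for three organisations. Those figures leave out the stated baseline adjustment and are upper bounds on the benefit; with it, the gain is about one point or turns into a small loss. Finally, a reader might take a wrong standard error to mean excess false positives. The error runs the other way.

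**Conclusion.** The point holds in a limited form, with moderate confidence. Organisation is the randomisation stratum, and the effect model names only the baseline outcome. If the model is run as stated and organisations differ, the standard error is overstated and the test is conservative, with type I error of roughly 3-4.5% in place of 5%. The effect is at the milder end of that range once baseline is in the model, and it is absent if organisations are alike. Only the more extreme scenarios without baseline adjustment fall lower (2.1% at the lowest). All these sizes rest on assumed numbers of organisations, an assumed split of the 0.04 ICC, equal cluster sizes and balance within organisations. The documents do not support the claims that stratification has been discarded, that false positives are inflated, or that about five points of power are at stake. The stated sample size is unaffected.

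**What to change.** In the Data analysis section of the effect evaluation, state that organisation, as the randomisation stratum, is a term in the primary and secondary mixed models alongside the baseline value, with the randomised unit as random intercept and participant as the repeated-measures level. This takes one sentence and no new data.

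The cost is one degree of freedom per extra organisation. With 12 clusters, the degrees of freedom fall from 10 to 12 − J − 1 for J organisations: 9, 8 and 5 for 2, 3 and 6. If there are many small organisations, or they do not differ, this can cost a few points of power. The form of the term should therefore be settled once the number of organisations is known and before outcome data are analysed.

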#### Process evaluation

##### Study design

To understand the success or failure of the implementation of the integrated Dutch WHPP and its activities, a process evaluation will be conducted among the clusters in the intervention condition. Two process evaluation models will be combined, as these complement each other [51, 52]. Using the framework of Wierenga et al. (2012), recruitment, reach, dose delivered, dose received, fidelity, satisfaction, maintenance and context will be evaluated. As implementation strategy and participants’ mental models are expected to play an important role in the success or failure of the implementation, these components from the framework of Nielsen and Randall (2013) will be added to the initial framework. Data will be collected by means of mixed methods, combining quantitative and qualitative methods.

